#### Sample size

We assume a 50% ongoing pregnancy rate within 12 months after tubal testing, with no difference between HSG or HyFoSy. When using a non-inferiority test at a 5% significance level, the total sample size will be guided by the fraction *f* of participants with discordant results (these will be randomized). In the randomized subgroup, the corresponding non-inferiority margin will then correspond to 2% divide by the fraction with discordant results *f* [14]. Assuming the fraction with discordant results is 7% [7], the non-inferiority margin in the discordant results will be 29%. To achieve 80% power to reject inferiority, we would then need to randomize 74 women with discordant results, and the total number to be included will be 1057 (74 divide by 7%). To account for a 10% loss to follow-up, we will include 1163 participants, resulting in 82 participants with discordant results.

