**Methods/design:**

We aim to compare the effectiveness and costs of management guided by HyFoSy or by HSG. Consenting women will undergo tubal testing by both HyFoSy and HSG in a randomized order during fertility work-up. The study group will consist of 1163 subfertile women between 18 and 41 years old who are scheduled for tubal patency testing during their fertility work-up. Women with anovulatory cycles not responding to ovulation induction, endometriosis, severe male subfertility or a known contrast (iodine) allergy will be excluded. We anticipate that 7 % (*N* = 82) of the participants will have discordant test results for HyFoSy and HSG. These participants will be randomly allocated to either a management strategy based on HyFoSy or a management strategy based on HSG, resulting in either a diagnostic laparoscopy with chromopertubation or a strategy that assumes tubal patency (intrauterine insemination or expectant management). The primary outcome is ongoing pregnancy leading to live birth within 12 months after randomization. Secondary outcomes are patient pain scores, time to pregnancy, clinical pregnancy, miscarriage rate, multiple pregnancy rate, preterm birth rate and number of additional treatments. Costs will be estimated by counting resource use and calculating unit prices.

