#### Statistical analysis

We will estimate and compare the proportion of women with an ongoing pregnancy leading to live birth within 12 months after inclusion for two strategies: one in which management in subfertile women undergoing tubal patency testing is guided by the results of HSG and a second strategy, in which management is guided by the results of HyFoSy. To estimate this proportion, we will have to combine the outcomes observed in the concordant group, in which management will be identical for the two strategies, and in the discordant group, in which women are randomly allocated to management based on HSG or management based on HyFoSy.

The proportion of women with an ongoing pregnancy leading to live birth for each strategy will be a weighted average of the proportions observed in two groups: the concordant group and the discordant group, where the patients in the discordant group have to be counted twice, to account for the randomization, since in half of the women in the discordant group management will be guided by the other test. Lu and Gatsonis [14] have shown that this estimate is unbiased, and have provided a closed form for the variance of this estimate. They have also shown that this paired design is more efficient than an unpaired comparison of test & management strategies, especially if the proportion of women with discordant results is low. The effectiveness of management based on HyFoSy relative to management based on HSG will be expressed as a relative risk and as an absolute difference, each with 95% confidence intervals. SPSS will be used to perform the statistical analysis.

The primary analysis will be a non-inferiority test, in which we want to exclude a decrease of 2% when relying on the HyFoSy results instead of on the HSG. No interim analysis will be performed.

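### The allowance for 10% loss to follow-up was made by multiplying by 1.1, so the target of 1163 women covers 9.1% loss; the effect on power is negligible

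*Protocol article*

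**What the plan says.** All the figures are in the Sample size section of the protocol article.

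- Event rate and true difference: "We assume a 50% ongoing pregnancy rate within 12 months after tubal testing, with no difference between HSG or HyFoSy".
- Significance level: "When using a non-inferiority test at a 5% significance level". Whether this is one-sided or two-sided is not said.
- Margin: 2 percentage points overall, divided by an assumed discordant fraction of 7%, and given as 29% within the discordant group.
- Requirement before loss: "we would then need to randomize 74 women with discordant results, and the total number to be included will be 1057", the total being 74 divided by 7%.
- Allowance for loss: "To account for a 10% loss to follow-up, we will include 1163 participants, resulting in 82 participants with discordant results".

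The section does not give the formula for the last step, and no other part of the article states a different rule for loss to follow-up. The Abstract repeats 1163 and 82 but mentions neither a loss allowance nor power.

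**The concern.** A loss rate is ordinarily a fraction of the women enrolled. To be left with n women after losing a fraction d, one enrols n / (1 − d). Multiplying by (1 + d) gives a smaller number, which falls short of n once the losses occur. The stated totals look like the product of that shortcut.

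The comparison of strategies is informed only by the small discordant group, because management is identical when the two tests agree. It is therefore worth checking whether the enrolment target, the 10% allowance and the requirement of 74 fit together, and whether any mismatch is large enough to matter for power.

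**Working it through.** **Inputs (Sample size section, except where noted).** Rate 50% in both strategies, difference 0; margin 29 points in the discordant group; power 80%; discordant fraction 7%; loss 10%. Equal allocation is implied by the Statistical analysis section, which says that half of the discordant women are managed by the other test. A one-sided 5% level is inferred because it reproduces the stated 74.

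**1. Reproduce the requirement.**
n per arm = 2 × 0.25 × (1.645 + 0.842)² / 0.29² = 36.76, rounded up to 37, so 74 in total. The unrounded total is 2 × 36.76 = 73.5.
Total to enrol before loss: 74 / 0.07 = 1057.1, stated as 1057.

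**2. Reproduce the inflated figures.**

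| Requirement | × 1.1 | Stated | ÷ 0.9 | Rounded up |
|---|---|---|---|---|
| 1057 | 1162.7 | 1163 | 1174.4 | 1175 |
| 74 | 81.4 | 82 | 82.2 | 83 |

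Multiplication by 1.1 matches both stated figures after rounding up. Division by 0.9 matches neither.

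**3. Run the stated target forward.**
- Retained at 10% loss: 1163 × 0.9 = 1046.7, against 1057.
- Analysable discordant women: 1046.7 × 0.07 = 73.3, against 74.
- Starting from the rounded 82: 82 × 0.9 = 73.8.
- Loss that 1163 covers: 1 − 1057/1163 = 9.1%.
- Check on the corrected total: 1175 × 0.9 × 0.07 = 74.0.

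**4. Effect on power.** With both rates at 50% and equal arms, the standard error of the difference is 1/√n, where n is the total number of discordant women analysed. Power = Φ(0.29 × √n − 1.645).

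| Discordant women analysed | Power |
|---|---|
| 74 (requirement) | 80.2% |
| 73.8 (82 less 10%) | 80.1% |
| 73.3 (7% of 1046.7) | 79.9% |

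**5. Scale against chance.** With 1163 women and a true fraction of 7%, the number of discordant women has mean 81.4 and standard deviation √(1163 × 0.07 × 0.93) = 8.7. The shortfall of 0.7 is less than a tenth of that.

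**The case against.** The strongest reply is that nothing of substance follows. The unrounded need is 73.5 women, and the stated 82 less 10% leaves 73.8, which still gives 80.1% power. Only the calculation that starts from 1163 dips below 80%, and 79.9% rounds to 80%. Other uncertainties are larger: chance variation in the discordant count, the 7% itself (taken from 5 of 73 women in one cohort, as the Background reports), and the rounding of the margin from 28.57 to 29 points, which moves power at 74 women from 79.2% to 80.2%. Recruitment was expected to end in August 2018, a few months after the article appeared in May 2018.

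All of this stands, and it settles the severity. It does not remove the mismatch: 1163 enrolled, 10% lost and 1057 retained cannot hold together.

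A reader might infer more than the document supports:

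- **That the trial misses its stated power.** The figures above do not bear this out; the change is from 80.2% to 79.9%.
- **That the shortcut was chosen to favour the trial.** Nothing shows intent, and 1162.7 and 81.4 were both rounded upward.
- **That the rounding is a further error.** Writing 1057.1 as 1057 and 81.4 as 82 is ordinary rounding in a planning estimate.
- **That the Abstract is also wrong.** It makes no statement about loss or power that 1163 could fail to meet.

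**Conclusion.** The point holds as a minor arithmetic correction. The Sample size section multiplies by 1.1 where a 10% loss among enrolled women calls for division by 0.9. The stated 1163 covers 9.1% loss. Against a true 10% allowance it is 12 women short (1175 − 1163, or 1.0%), about 0.7 of a discordant woman, with power of 79.9% instead of 80.2%. This does not make the trial materially underpowered, and no analysis, margin or conclusion changes.

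The result assumes that the 10% refers to women enrolled, that loss is equally common in concordant and discordant women, and that the section's own inputs apply (50% in both strategies, 29-point margin, one-sided 5%, 7% discordant). The enrolment arithmetic does not depend on the sidedness or the rounding of the margin. The power figures do: with the unrounded margin they are 79.2% at 74 women and 78.8% at 73.3, so the difference due to the loss step stays just as small. Lowest severity.

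**What to change.** Keep enrolment at 1163 and reword the last sentence of the Sample size section. It should say that 1163 women (about 81 discordant at 7%) allow for about 9% loss to follow-up, and that at 10% loss about 73 discordant women would be analysable, with power of about 80% (79.9%). For reference, the total that matches a true 10% allowance is 1175, with 83 discordant women when 74 / 0.9 is rounded up.

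The cost is one sentence. No extra participants are needed, and the 1163 in the Abstract stays as it is. The only downside is that the stated allowance becomes slightly less generous.

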##### Economic evaluation

The economic analysis will be performed alongside the clinical trial and will estimate costs from a third-party payer as well as from a societal perspective. A distinction will be made between costs of medical interventions (direct costs) and costs resulting from productivity losses (indirect costs), obtained from the HLQ questionnaires. Standardized units will be calculated for all centers based on actual resource use made during the trial. The economic evaluation will be designed as a cost-effectiveness analysis with the costs per ongoing pregnancy within 12 months as the primary outcome. The cost-effectiveness of each strategy will be presented as cost per live birth. A discounting rate of 4% will be used in the analysis. The incremental cost-effectiveness ratio (ICER) of a strategy based on HyFoSy as compared to a strategy based on HSG will be estimated as the ratio between difference in costs between the strategies and the difference in pregnancy rates, and reflects the extra costs required to obtain one additional live birth. The economic analyses will be presented in a separate report.

##### Ethical consideration

This study is approved by the National Central Committee on Research involving Human Subjects (CCMO – NL50484.029.14), by the ethics committee of the VU Medical Centre Amsterdam (Ref. No. 2014/454) and by the boards of all participating hospitals. The trial is registered in the Dutch Trial Register (NTR 4746, http://www.trialregister.nl).

## Discussion

HSG is the most widely used outpatient tubal test during fertility work-up. It was introduced in 1914 and still serves as an accurate diagnostic test, but may be painful, implies exposure to ionizing radiation and is expensive. HyFoSy is a new technique and proposed as a more patient friendly alternative for HSG as a first line office tubal patency test. No large trials have been published comparing HSG with HyFoSy. lf HyFoSy is as accurate as HSG in diagnosing tubal patency, it will lead to comparable management decisions and similar pregnancy outcomes and HSG could be substituted by HyFoSy for tubal patency testing during fertility work-up. Since approximately 20,000 HSGs are performed each year in the Netherlands and based on a cost difference between HyFoSy and HSG of around €100, replacing HSG by HyFoSy could result in substantial cost reduction.

The use of two physicians for the two tubal patency tests can be a logistical challenge for smaller district centers. However, this blinding is an essential aspect for the objectivity of test results of the whole study population and the strategy comparison of the randomization in case of discordance. Further randomization and allocation concealment through a web based randomization program reduces the chance for selection bias.

The final choice between HyFoSy and HSG will also depend on the direct therapeutic effect of both procedures. A recent large randomized clinical trial confirmed the long-stated hypothesis that HSG with oil-soluble contrast directly improves ongoing pregnancy and live birth rates [15]. Thus, if the FOAM study shows that HyFoSy is cost-effective over HSG in terms of diagnostic accuracy, the next question to be answered is if tubal flushing with oil after HyFoSy improves pregnancy rates.

The additional burden for women included in the study follows from undergoing one additional tubal patency test. This can lead to reluctance in taking part in the FOAM study. Offering the two tests on the same day, explaining women that HyFoSy is a more patient-friendly and less painful examination then HSG [6] and pointing out the potential benefit of HyFoSy for patients in the future, might overcome this.

If this trial shows that the fertility work-up with tubal testing based on HyFoSy is an efficient and effective alternative to HSG, the results may lead to evidence-based changes in national and international guidelines.

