## Background

Subfertility, defined as the inability to conceive within 12 months of unprotected intercourse, affects 1 out of 6 couples trying to get pregnant [1]. Traditionally, the diagnostic work-up for subfertility includes tests to assess tubal status, among which hysterosalpingography (HSG) and diagnostic laparoscopy with chromopertubation (DLS) are the most established tests [2]. HSG is still the test of first choice during the fertility work-up in many clinics in the Netherlands. In case bilateral tubal pathology is suspected, a DLS is performed which is considered the clinical reference standard. DLS is an invasive test under general anesthesia that allows direct visualization of the pelvis, including fallopian tubes, ovaries and uterus. However, there is a risk for visceral damage, intra-abdominal bleeding and risks related to general anesthesia. Initially, hysterosalpingo-contrast sonography (HyCoSy) has been proposed as an alternative for HSG as a first line office tubaI patency test. The accuracy of HyCoSy is comparable to that of HSG [3, 4]. However, the commonly used echogenic medium for HyCoSy Microcrystalline suspension (Echovist®, Schering AG, Berlin, Germany), is no longer available. In 2011, hysterosalpingo-foam sonography (HyFoSy) was introduced as a new technique for tubal patency testing and an alternative for HyCoSy [5]. This imaging technique is comparable to HyCoSy, but it uses foam instead of gel.

The advantages of HyFoSy over HSG are manifold; with HyFoSy there is no radiation exposure which makes it a more patient friendly examination compared to HSG. In addition, the HyFoSy procedure is less painful as well as less time consuming compared with HSG [6] and a HyFoSy can be performed by the gynecologist during regular office hours, establishing the fertility work-up in a one stop clinic.

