### Study procedures

All consenting participants will be scheduled for both HyFoSy and HSG. The order of these tests will be determined by randomization. Both tubal patency tests will be done within the two weeks of the follicular phase of the cycle after complete cessation of menstrual bleeding. The physician performing the HSG will be blinded for the results of the previously performed HyFoSy and vice versa. Test results of HyFoSy and HSG will be classified as normal, one-sided tubal pathology or double-sided tubal pathology.

lf the results of both tubal patency tests are concordant, the planned fertility treatment will be based on the test results in accordance with the current Dutch guideline [2]. Participants with one or two patent tubes at HyFoSy and HSG will be treated according to their prognosis for natural conception based on the model of Hunault [10]. In case the chance of natural conception within the following 12 months exceeds 30%, participants will be counseled for expectant management for 6-12 months. In case the chance is less than 30%, participants will be treated with intrauterine insemination (IUI) eventually followed by in vitro fertilization (IVF). In case HyFoSy and HSG are concordant in the diagnosis of suspected bilateral tubal occlusion, participants will be scheduled for DLS, followed by IVF in case bilateral tubaI occlusion is confirmed. In case of one-sided or two-sided patency during DLS the subsequent fertility treatment will also be based on the Hunault prognosis for natural conception.

Participants in whom the results of the tubaI patency tests HyFoSy and HSG are discordant will subsequently be included in a randomized trial in which they will be randomized between management based on the results of HyFoSy or management based on the results of HSG.

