##### Recruitment, consent and randomization, collection of data

Eligible women receive oral and written information during their regular outpatient visit by the attending gynecologist or fertility doctor. Women will be contacted by telephone for further information by the investigator. Women who agree to participate will be asked to sign written informed consent, of which they will receive a copy at their next visit, when the informed consent form will also be signed by the investigator, supervising gynecologist, the attending registrar or fertility doctor. Women who decline randomization will be offered the standard tubal patency testing with HSG or DLS, depending on the standard management policy in the clinic. Women refusing participation are registered.

Consenting eligible women undergo a HyFoSy as well as an HSG in a random order. Randomization is stratified for each center and will be performed after baseline data have been entered in a central web-based system that is available in our research consortium (ALEA) with the use of a permuted block design. Randomization is performed with only initials and year of birth of the participants. Linking personal data to the study number can only be performed in the local participating centers. Written informed consent forms are stored in every center in a lockable room. All forms and data will be archived for 15 years in the participating centers.

When there is discordance between the results of HSG and HyFoSy participants will be randomly allocated by the web based randomization program (ALEA) for management based on either HyFoSy or HSG.

After inclusion, all measurements will be systematically recorded using an electronic Clinical Report Form. These electronic forms will be stored in a digital database. Data are handled confidentially and, whenever possible anonymously. A subject identification code list will be used to link the data to the subject, where it is necessary to be able to trace data to an individual subject. The code will not be based on the woman’s initials and birth date, the key to the code will be safeguarded by the local investigator. The handling of personal data will comply with the Dutch Personal Data Protection Act (in Dutch: De Wet Bescherming Persoonsgegevens, Wbp).

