##### Outcome measures

The primary outcome for the comparison of the two strategies is ongoing pregnancy leading to live birth within 12 months after inclusion. Ongoing pregnancy rate is defined as an intrauterine pregnancy with a positive heartbeat during ultrasound examination between 10 and 12 weeks of pregnancy. Secondary outcomes are pain scores (measured by Visual Analogue Scale (VAS) scores), time to pregnancy, clinical pregnancy (defined as an ultrasound visible gestational sac with or without heartbeat), miscarriage (defined as the presence of non-vitality on ultrasound or spontaneous loss off pregnancy), multiple pregnancy (defined as a pregnancy of two or more fetus), preterm birth rate (defined as a delivery before 37 weeks of pregnancy), quality of life and absence of work.

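### Suggesting at recruitment that HyFoSy hurts less than HSG opens the patient-rated pain comparison to expectation bias in favour of HyFoSy

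*Protocol article*

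**What the plan says.** Under Discussion, the protocol article notes that women in the study bear the burden of one extra test: "This can lead to reluctance in taking part in the FOAM study". It names three measures that might help: offering both tests on one day, pointing to the benefit for future patients, and "explaining women that HyFoSy is a more patient-friendly and less painful examination then HSG".

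Under Outcome measures the text reads "Secondary outcomes are pain scores (measured by Visual Analogue Scale (VAS) scores", and the Abstract makes clear that the patient is the rater: "Secondary outcomes are patient pain scores". Pain comes first in both lists of secondary outcomes.

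The comparison is within women: "Consenting eligible women undergo a HyFoSy as well as an HSG in a random order" (Recruitment, consent and randomization, collection of data). The only masking described concerns the operator and the other test's result: "The physician performing the HSG will be blinded for the results of the previously performed HyFoSy and vice versa" (Study procedures).

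The Background already treats the pain question as answered, citing an earlier study: "the HyFoSy procedure is less painful as well as less time consuming compared with HSG".

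**The concern.** A recruitment message reaches women before they have either test and so before they rate either. If it says that one test hurts less, it supplies an answer to a question that the trial asks the same women. Pain on a visual analogue scale is subjective. One test uses X-ray and the other transvaginal ultrasound, so a woman can hardly be unaware which she is having. Any expectation created would lower HyFoSy scores relative to HSG scores.

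At stake is one secondary outcome that supports the case for HyFoSy. The Abstract describes HyFoSy as thought to be cheaper and more patient friendly, and the Background gives less pain as one of its advantages. The Discussion hopes that the results will change guidelines. A modest pain difference could be cited in that context as a trial finding although it might owe something to what women were told beforehand.

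**Working it through.** **The plan's own figures.** The article gives no sample size, standard deviation or expected difference for pain. Its only calculation is for the primary outcome: "When using a non-inferiority test at a 5% significance level", with 50% in both strategies, a margin of 29% in the discordant group and 80% power.
- Per arm: 2 × 0.5 × 0.5 × (1.645 + 0.842)² / 0.29² = 36.8, rounded up to 37, so 74 randomised.
- Total: 74 / 0.07 = 1057, and 1057 × 1.1 = 1163.

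This reproduces the stated numbers, reading the 5% as one-sided. No pain quantity enters, so the primary sample size is unaffected.

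**Do the described safeguards deal with expectation?**
- *Random order.* Write the pain score as test effect + position effect + expectation effect. Randomising the order balances position across the two tests. An expectation tied to the test is present whether HyFoSy comes first or second, so it stays in the HyFoSy minus HSG difference.
- *Operator masking.* This keeps one operator from knowing the other test's result. It protects the reading of tubal patency and has no bearing on what the woman expects to feel.
- *Within-woman design.* It removes differences between women in general pain reporting, but not an expectation that differs between the two tests.

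The article describes no other safeguard for the pain score.

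**Would the sample size protect against a small shift?** This part is an illustration. Assumptions not in the documents: a 100 mm scale, a within-woman SD of the difference of 20 to 30 mm, no true pain difference, a two-sided 5% test, and an expectation shift b in favour of HyFoSy. The number of pairs is taken as 1057, the article's total before the allowance for loss.
- SE = SD / √1057 = SD / 32.5, which is 0.62 mm (SD 20), 0.77 mm (SD 25) and 0.92 mm (SD 30).
- Smallest observed difference reaching significance: 1.96 × SE = 1.2 to 1.8 mm.
- Chance of a significant result = Φ(b/SE − 1.96) + Φ(−b/SE − 1.96). Nearly all of it lies in the first term, the direction favouring HyFoSy.

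| Shift b | SD 20 mm | SD 25 mm | SD 30 mm |
|---|---|---|---|
| 1 mm | 37% | 26% | 19% |
| 2 mm | 90% | 74% | 58% |
| 3 mm | 99.8% | 97% | 90% |

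With 1163 pairs the ranges are 21% to 40% (1 mm), 62% to 93% (2 mm) and 93% to 99.9% (3 mm). The table shows what a shift of a given size would do. It does not show that the message produces such a shift.

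**How many women could still be given neutral wording?** Recruitment began in June 2015 and was expected to end in August 2018 (Recruitment, consent and randomization, collection of data); the article is dated 9 May 2018. From 1 June 2015 that is 35.3 months elapsed, out of 38 (1 August) to 39 (31 August). Assuming even accrual, the women still to come number between 1163 × 2.7/38 = 83 and 1163 × 3.7/39 = 110.

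**The case against.** The sentence is a suggestion in the Discussion of what might overcome reluctance. The recruitment section mentions oral and written information and a telephone call, and it contains no message about pain. The patient leaflet is not shown. A reader might infer that all women were told HyFoSy hurts less and that the pain comparison is therefore biased. The documents do not support that: they do not establish what was said, to whom or how uniformly, and they give no measured effect. This stands, and limits the point to a risk with a clear direction.

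It can also be said that women may arrive with expectations anyway, since X-ray and ultrasound cannot readily be disguised. That stands too. Neutral wording would reduce the problem without abolishing it, and what the message adds cannot be isolated.

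Third, pain is not the criterion for adopting HyFoSy. The Background asks for live-birth outcomes at least as good at lower cost, and it ties patient-friendliness first to the absence of radiation. This is correct, and it keeps the point to one secondary outcome.

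Finally, the statement rests on an earlier study, and women may properly be told of existing evidence. The article, however, uses it as an inducement and states it as settled, while the same Discussion says that no large trial has compared the two tests. Neutral information can mention earlier evidence and still present relative pain as a study question.

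**Conclusion.** The point holds as a risk of bias. The article suggests giving prospective participants the expected answer to a patient-rated secondary outcome, and none of the safeguards it describes acts on that expectation. The direction is towards HyFoSy. The size cannot be determined from the documents. The table rests on an assumed scale, SD and shift, and supports one conclusion only: a trial this large would often declare a shift of 2 to 3 mm significant, so statistical significance alone would not distinguish a small true difference from a reporting effect. A large observed difference would be harder to attribute to the message, but the documents give no basis for a threshold.

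The primary outcome, the non-inferiority margin and the sample size are not touched.

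**What to change.** Remove the statement that HyFoSy is less painful from the recruitment approach. Tell women neutrally that both tests can cause discomfort and that which of them hurts less is one of the study's questions.

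For women already recruited under the message, report the pain comparison as open to expectation bias in favour of HyFoSy, and do not take a small difference on the scale as evidence that HyFoSy is less painful.

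A comparison of women recruited before and after the change should not be the main remedy. With roughly 80 to 110 women afterwards it would be imprecise, and it would be confounded with calendar time and possibly with the mix of centres.

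The cost is a revised information text, possibly slightly slower recruitment in the remaining months, and a more cautious conclusion on pain.
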